**Methods:**

A retrospective comparative cohort study will be conducted in a level II trauma center (Zaandam Medical Center). Patients who experienced a Dancer’s fracture in the period of 2012 to 2021 will be included and divided into 2 cohorts—the conservative (2012-2015) and operative (2016-2021) treatment cohorts. The primary outcome will be the differences in percentages of delayed union and nonunion between the two groups. The secondary outcomes will be the percentage of primary conservative treatment failure, the need for secondary operative treatment, complications (infection and hardware failure), and functional outcomes. If 118 patients are included in each group, sufficient power is expected to be reached, depending on the age distribution of patients. The percentages of delayed union and nonunion among the two groups will be calculated and statistically compared via chi-square statistics. A logistic regression analysis will be used to investigate possible associations between patient characteristics and failed conservative treatment. A Mann-Whitney *U* test will be used to compare functional outcomes between groups. An independent, 2-tailed *t* test will be used to compare mean 12-Item Short Form Survey scores if they are normally distributed, and a Wilcoxon rank sum test will be used if they are nonnormally distributed.

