### Study Design and Setting

Our study will be a retrospective cohort study. The researchers will be provided with records and diagnostic health insurance codes by the hospital’s medical administration. These codes represent patients with foot injuries (codes 237 and 238 for metatarsal and tarsal fractures, respectively) over the past 10 years in a single, regional, level II trauma center—the Zaandam Medical Center, Zaandam. These cases will be retrospectively analyzed to select oblique diaphyseal fractures of the fifth metatarsal bone, which are known as *Dancer’s fractures*. Since 2016, in our hospital, the preferred treatment changed from predominantly conservative treatment to mostly operative treatment. Therefore, the comparison of 2 historic cohorts will be made—the conservative treatment cohort (2012-2015) versus the operative treatment cohort (2016-2021).

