### Recruitment

A list of all foot fracture–related diagnostic health insurance codes in the Zaandam Medical Center dating from 2012 to 2021 will be provided by the hospital’s medical administration. All corresponding radiographs of the foot will be reviewed by 2 trauma surgeons to identify Dancer’s fractures. Patient characteristics such as age and sex, as well as fracture characteristics such as comminution, dislocation, the side of injury, and the occurrence of delayed union and nonunion, will be extracted from the electronic patient records manually by the researcher. Delayed union and nonunion are defined as absent or incomplete fracture healing after 3 and 6 months, respectively, and they will be assessed by reviewing the radiographs. The given treatments (cast vs surgery) and occurrence of complications (infection and hardware failure) will also be extracted from the electronic patient records manually by the researcher. The cohort will be divided into the following two groups: the conservative treatment cohort (2012-2015) and operative treatment cohort (2016-2021).
Patients will receive a letter about providing informed consent. The letter will state that after they provide consent, a researcher will call them. Patients will be asked if they underwent secondary surgery in another hospital and be asked to provide data that are missing from the electronic patient files, such as the mechanism of injury and smoking status at the time of injury.

Patients will also be asked to complete the 12-Item Short Form Survey (SF-12) questionnaire and to rate their functional outcomes by using 1 of the following 3 categories: (1) no more complaints or pain, (2) minor complaints or pain without an impact on daily living, and (3) significant complaints or pain with an impact on daily living [16].

If patients are lost to follow up, it will be assumed that they did not experience delayed union, nonunion, or other complications.

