### Outcomes

The primary outcome will be the delayed union and nonunion rates in the primary operative treatment group versus those in the conservative treatment group. The secondary outcomes will be the percentage of initial conservative treatment failure, which will be determined based on the percentage of patients who needed surgery after initially being treated conservatively; the number of patients who experience complications (infection and hardware failure); and associations between patient characteristics and failed initial conservative treatment. Functional outcomes—the complaints and impacts on daily living that are reported and experienced by patients—will also be secondary outcomes. These will be measured based on patients’ responses to the SF-12 and 3 categories (no more complaints or pain, minor complaints or pain without an impact on daily living, and significant complaints or pain with an impact on daily living).

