## Results

Approximately 2667 potentially relevant health insurance codes from a period of 10 years (2012-2021) will be extracted from the hospital’s digital register. To date, 2134 codes have been extracted. We expect to find a total of 236 Dancer’s fractures, of which approximately 50% (n=118) have been intentionally treated conservatively and 50% (n=118) have been primarily treated operatively. Based on our hypothesis and daily practice experience, it is expected that delayed union and nonunion rates will be higher in the conservative treatment group.

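### The two comparison groups are formed by calendar period in some sections and by initial treatment in others; the two rules do not coincide, and off-pattern patients are not classified

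*Protocol article*

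**What the plan says.** Three places in the protocol article form the groups by calendar period.

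- Abstract, Methods: patients are "divided into 2 cohorts—the conservative (2012-2015) and operative (2016-2021) treatment cohorts".
- Study Design and Setting: "Therefore, the comparison of 2 historic cohorts will be made—the conservative treatment cohort (2012-2015) versus the operative treatment cohort (2016-2021").
- Recruitment: "The cohort will be divided into the following two groups: the conservative treatment cohort (2012-2015) and operative treatment cohort (2016-2021").

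Two places describe the groups by the treatment first given.

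- Outcomes, for the primary outcome: "delayed union and nonunion rates in the primary operative treatment group versus those in the conservative treatment group", with no years attached.
- Results, for expected numbers: "approximately 50% (n=118) have been intentionally treated conservatively and 50% (n=118) have been primarily treated operatively".

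The Sample Size section attaches the same figure, about 118, to each cohort. Statistical Analysis applies a chi-square test to the two groups without saying which definition is meant.

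The Introduction and Study Design and Setting describe a shift in preference, not a clean switch: "the preferred treatment changed from predominantly conservative treatment to mostly operative treatment". Recruitment also says that the treatment given (cast or surgery) is extracted for each patient, but no section uses that variable to assign groups.

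**The concern.** The two rules give the same groups only if every 2012-2015 patient had a cast and every 2016-2021 patient had primary surgery. The article's own description rules out relying on that. A patient operated on in 2014 counts as conservative under one rule and operative under the other; the reverse holds for a patient given a cast in 2018.

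What is at stake is the meaning of the primary result. The objective and primary outcome are worded as operative versus conservative treatment. If the year rule is followed literally, healing failures after a cast in the later period count against surgery, and early operations are credited to casting. The result would then be a before-and-after policy contrast reported under treatment labels. The article intends the findings to inform the size and design of a randomised trial and individual treatment decisions. Both uses need to know which contrast was estimated.

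**Working it through.** **Inputs.** From Sample Size: 236 patients, about 118 per cohort; nonoperative rate 3% to 9% in the general population and 35% at age 40 or over; operative rate 4% to 7%; stated power 34.3% and 100%. From Results: 118 conservative and 118 operative by treatment. Periods: 4 years (2012-2015) and 6 years (2016-2021). Assumptions, because the article does not state them: two-sided alpha 0.05, yearly incidence and crossover shares.

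**Step 1. Reproduce the stated power.** Take 9% vs 4%, 118 per group, pooled-variance normal approximation.

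- Mean rate = 0.065.
- SE under the null = √(2 × 0.065 × 0.935 / 118) = 0.0321.
- SE under the alternative = √((0.09 × 0.91 + 0.04 × 0.96) / 118) = 0.0319.
- Power = Φ((0.05 − 1.96 × 0.0321) / 0.0319) = Φ(−0.404) = 34.3%.

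This matches. For 35% vs 4% or 7% the result is above 99.9%, which matches the stated 100%. The arithmetic is sound, but these are treatment-specific rates, so the calculation assumes unmixed groups.

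**Step 2. Effect of mixing.** Let pC and pO be the event rates after conservative and operative treatment, e the share operated on in the early period, and l the share treated conservatively in the late period.

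- Early rate = (1 − e)pC + e·pO.
- Late rate = (1 − l)pO + l·pC.
- Difference = (1 − e − l)(pC − pO).

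So, without secular trend and with mixing unrelated to prognosis, the period contrast keeps the fraction 1 − e − l of the treatment effect.

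**Step 3. Illustration with constant incidence.** The periods would hold 236 × 4/10 = 94.4 and 236 × 6/10 = 141.6 patients. Holding the total conservatively treated at 118, l = (118 − 94.4(1 − e)) / 141.6.

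- e = 0%: l = 23.6/141.6 = 16.7%; retained 83%.
- e = 10%: l = 33.04/141.6 = 23.3%; retained 67%.
- e = 20%: l = 42.48/141.6 = 30.0%; retained 50%.

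Power of the chi-square test by exact binomial enumeration at 94 and 142:

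| Early operated | Late conservative | 9% vs 4% becomes | Power | 35% vs 7% becomes | Power |
|---|---|---|---|---|---|
| Groups by treatment, 118/118 | none | 9.0% vs 4.0% | 35% | 35.0% vs 7.0% | about 100% |
| 0% | 16.7% | 9.0% vs 4.8% | 23% | 35.0% vs 11.7% | 99% |
| 10% | 23.3% | 8.5% vs 5.2% | 16% | 32.2% vs 13.5% | 93% |
| 20% | 30.0% | 8.0% vs 5.5% | 11% | 29.4% vs 15.4% | 73% |

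The unequal period sizes are not the cause: under the Step 1 approximation, an unmixed 94/142 split gives 36.3% for 9% vs 4%.

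**Step 4. Illustration with 118 in each period.** If each period also holds 118, then 118 conservatively treated in total forces e = l = m, and the retained fraction is 1 − 2m. For m = 10%, 20% and 30%, power (normal approximation) is 23.7%, 15.2% and 9.0% for 9% vs 4%, and 99.1%, 89.2% and 56.1% for 35% vs 7%. The conclusion does not depend on constant incidence.

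**The case against.** The strongest reply is that only one allocation rule is actually written, by year, and it appears three times. Outcomes and Results may simply reuse the labels conservative and operative as shorthand for those cohorts. Study Design and Setting argues its way to the historic comparison, and comparing periods is a recognised way to limit confounding by indication. That matters here because the Introduction names age, osteoporosis, angulation and comminution as factors in the choice of treatment. The study is also retrospective and meant as a first insight.

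Much of this stands. A period comparison is legitimate, but it must be called one, and the article presents it as a comparison of treatments. The shorthand reading fits Outcomes better than Results, where the counts refer to patients intentionally treated one way or primarily treated the other.

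Some stronger inferences should be resisted.

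- A reader might infer that the article's own numbers prove about 24 conservatively treated patients (17%) in the later cohort. They do not. No yearly counts are given, and Sample Size may mean 118 per period.
- A reader might infer that two rival primary analyses were planned. The article shows an ambiguity, not two prespecified analyses.
- A reader might infer that conservative-treatment failure would lose the later cast patients. Outcomes defines it by initial treatment with no limit on years, so this is not supported.
- A reader might infer that grouping by treatment is the only correct choice. It removes the dilution but is more exposed to confounding by indication.

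**Conclusion.** The inconsistency is real and affects the primary comparison. The written allocation rule is by period, the primary outcome and expected counts are worded by treatment, the article says that the two do not fully coincide, and off-pattern patients are left unclassified. This conclusion rests on the text alone.

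The size rests on assumptions. The crossover shares are unknown; two-sided 0.05, 118 conservatively treated patients and, for the 94/142 figures, constant incidence are assumed. Within that range, 83% down to 50% of the effect is retained. The loss of power is heavy at 9% vs 4%, where the article already discloses low power. At 35% vs 7% it is slight unless crossover is substantial, although the estimate is still diluted. Dilution towards no difference is not guaranteed: secular change, or treatment choice related to prognosis, could move the result either way.

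**What to change.** Before outcomes are analysed, state one group definition for the primary outcome and make the Abstract, Study Design and Setting, Recruitment, Outcomes, Sample Size and Results agree with it. Either choice is defensible:

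- (a) group by initial treatment (cast or surgery), adjusted for recorded confounders such as age, displacement and comminution; or
- (b) group by period, explicitly labelled as a comparison of 2012-2015 policy with 2016-2021 policy.

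Prespecify the other definition as a companion analysis. State how an early patient with primary surgery and a late patient with a cast are classified. Report the share operated on in each period, and give expected numbers both by treatment and by period. State expressly that conservative-treatment failure is computed on all initially conservatively treated patients from both periods.

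The cost is wording and one extra analysis, since treatment given is already being extracted. Option (a) is more exposed to confounding by indication and option (b) to dilution and secular change, so both results should be reported.

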### Ethical Considerations

All collected data will be processed and filed anonymously on the hospital’s secured servers. Data will be stored in separate files. One file will contain coded patient information, and a second file will contain all variables and diagnoses that are linked to these codes. The key to this code will be safeguarded by the head researcher. Patients will be asked via mail to provide informed consent prior to being contacted by telephone. The study is not subject to the Medical Research Involving Human Subjects Act (*Wet medisch-wetenschappelijk onderzoek met mensen* [WMO]). This Dutch act states that official medical ethics approval is not needed as long as patients are not subjected to invasive maneuvers, a specific code of conduct is used, and questionnaires do not contain sensitive questions (eg, those concerning mental health status) [18,19]. Confirmation of this status (*niet-WMO-verklaring*) will be obtained from the regional medical ethics committee.

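### Surgery in another hospital is visible only for patients who consent and are telephoned, while conservative failure is a percentage of all initially conservative patients, so the rate can only be at or below the truth

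*Protocol article*

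**What the plan says.** Under Recruitment, the given treatment and complications "will also be extracted from the electronic patient records manually by the researcher". Surgery in another hospital has a different source: "Patients will be asked if they underwent secondary surgery in another hospital". The call depends on consent: "The letter will state that after they provide consent, a researcher will call them". Ethical Considerations confirms the order: "Patients will be asked via mail to provide informed consent prior to being contacted by telephone".

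The same call is to supply "data that are missing from the electronic patient files, such as the mechanism of injury and smoking status at the time of injury".

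Under Outcomes, failure of initial conservative treatment is "determined based on the percentage of patients who needed surgery after initially being treated conservatively". The denominator is not limited to patients who were interviewed.

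Recruitment also treats patients lost to follow-up as free of the healing outcomes and of other complications. That rule does not name secondary surgery. Strengths and Limitations mentions recollection bias and unstandardized follow-up, but not that outside surgery goes unseen in patients who do not respond.

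**The concern.** The numerator and denominator of the failure rate rest on different levels of information. Everyone in the conservative group is in the denominator, but an operation elsewhere reaches the numerator only if the patient returns consent and is reached by telephone.

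The rate serves the second study objective (how many conservatively treated fractures later needed surgery), and the same outcome is the dependent variable for the third (patient characteristics linked to failure). The article intends the data for the sample size of future prospective studies, and for grant applications and patient selection. An understated failure rate would carry into those uses.

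A second, separate issue concerns the third objective. Where the chart lacks smoking status, it is supplied from memory by patients who consent, after they know how treatment ended. Comparison With Prior Work expects worse healing in smokers, so readers will look at this predictor.

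**Working it through.** **The plan's own figure.** The article gives no figure for the failure rate. Its only related calculation is the power for the primary outcome, 34.3%. That reproduces with 118 per group, 9% versus 4%, pooled variance and two-sided 5% (alpha assumed):

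- null SE = √(2 × 0.065 × 0.935 / 118) = 0.0321
- alternative SE = √((0.09 × 0.91 + 0.04 × 0.96) / 118) = 0.0319
- power = Φ((0.05 − 1.96 × 0.0321) / 0.0319) = 34.3%

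The present point neither depends on this figure nor changes it.

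**Inputs for the failure rate.**

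- n = 118 conservative patients (Sample Size and Results).
- F, the true failure rate: not given; 10% and 20% used for illustration.
- e, the share of secondary operations done elsewhere and not visible in this hospital's records: not given; 5% to 30% assumed.
- r, the share of those patients who consent and are reached: not given; 40% to 80% assumed.

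**Formula.** In-house failures are all seen: F(1 − e). Outside failures are seen only in those reached: F × e × r. With all conservative patients in the denominator,

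observed = F × [(1 − e) + e × r] = F × [1 − e(1 − r)].

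This equals F only if e = 0 or r = 1; otherwise it is lower.

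**Results.**

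| e | r | Observed / true | F = 10%: observed (missed of 118) | F = 20%: observed (missed of 118) |
|---|---|---|---|---|
| 5% | 80% | 1 − 0.05 × 0.20 = 0.99 | 9.9% (0.1) | 19.8% (0.2) |
| 20% | 60% | 1 − 0.20 × 0.40 = 0.92 | 9.2% (0.9) | 18.4% (1.9) |
| 30% | 40% | 1 − 0.30 × 0.60 = 0.82 | 8.2% (2.1) | 16.4% (4.2) |

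For scale, the standard error of a 10% rate in 118 patients is √(0.10 × 0.90 / 118) = 2.8 points, so the largest shortfall at F = 10% (1.8 points) is smaller than one standard error.

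**If the rate were restricted to respondents.** The downward bias gives way to response selection, which can go either way. With F = 20%:

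- 80% response in failures, 50% in others: 0.16 / (0.16 + 0.40) = 28.6%
- 50% response in failures, 60% in others: 0.10 / (0.10 + 0.48) = 17.2%

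**Events available for a respondent-only model.** At F = 10%, 55% response gives 118 × 0.55 ≈ 65 patients and about 6.5 failures; 40% response gives about 47 patients and 4.7 failures. Neither supports a multivariable model.

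**Recall interval.** The conservative cohort was injured in 2012 to 2015. If calls follow the 2012 to 2021 window, recall spans about 6 to 10 years.

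**The case against.** The article never says that a non-respondent counts as free of surgery elsewhere. The loss-to-follow-up rule does not list secondary surgery, and complications are glossed as infection and hardware failure. If the rate were computed among interviewed patients, its bias would be selection, of unknown direction. This stands as a limit on certainty: the downward direction follows from the literal definition under Outcomes, not from a stated rule for non-respondents.

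The size is unknown. Few operations may have been done elsewhere, and charts may record some through correspondence. Asking by telephone also captures more than records alone would. All of this stands. A reader might infer that about a third of failures are lost; half of operations elsewhere with 40% response would give 1 − 0.50 × 0.60 = 0.70, a 30% loss. Nothing in the article supports such inputs.

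A reader might also infer that the smoking data lower the failure rate. They cannot, because smoking status is not part of that rate. Nor is recall the main source: the chart comes first, and the limitations section discloses recollection bias.

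Finally, source flags and sensitivity models are details that an article may leave to a fuller plan, and their absence is no fault. What remains is that the stated data source and the stated denominator do not match.

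**Conclusion.** The point holds in a limited form. Followed as written, the plan pools patients whose outside surgery is known with patients whose outside surgery cannot be known, and the resulting failure rate is at or below the true rate. Over the assumed range (e 5% to 30%, r 40% to 80%) it is 82% to 99% of the truth. F, e and r are all assumptions, and the bias may be negligible. The direction rests on keeping all initially conservative patients in the denominator.

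The smoking issue is separate. Recalled or missing values that depend on consent can distort the regression on patient characteristics; their effect cannot be quantified from the article. Both issues touch secondary outcomes only, and the primary comparison and its power calculation are unaffected by this point.

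**What to change.** 1. Report two failure rates. (a) Secondary surgery in this hospital among all initially conservative patients, from records. (b) Surgery in any hospital among telephone respondents only, with the response rate and a sensitivity range for non-respondents. Do not count non-respondents as free of surgery elsewhere.
2. Label (a) for what it is: consistently ascertained, but a count of in-house surgery. With F = 20% and e = 20% it would be 0.20 × 0.80 = 16%.
3. Fit the predictor model on (a) only, and describe (b) without a multivariable model. Even (a) may carry few events: at F = 10% and e between 5% and 30%, 11.8 × 0.95 to 11.8 × 0.70, or about 11 to 8.
4. Record whether smoking status came from the chart or the telephone, and repeat the model with chart-recorded values as a sensitivity analysis if numbers allow.

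The cost is a source flag and an extra table; no new patients or data sources are needed. The downside is that (b) rests on fewer patients, has a wider interval, and is open to response selection in either direction, so it should be read beside (a) and not in its place.

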### Sample Size

Based on the limited available literature, delayed union and nonunion have been found in 3% to 9% [7,8] of patients in the general population who were treated nonoperatively. For patients aged ≥40 years, the delayed union rate for nonsurgical treatment is 35% [5]. This rate ranges from 4% to 7% for patients who were treated operatively [11,12]. It is expected that 236 patients will be included in our study, with approximately 118 in each cohort. Based on a post hoc power analysis, a power of 34.3% can be achieved by recruiting patients from the general population, and a power of 100% can be achieved by recruiting patients aged ≥40 years. As the incidence rates of delayed union and nonunion are unreliable in the available (limited) literature, the post hoc power analysis showed large differences in power—a problem that is often encountered [17]. However, our cohort will be the largest cohort of patients with Dancer’s fractures to date. Based on our clinical experience, we also believe that the incidence of delayed union and nonunion might be high in the nonoperative treatment cohort. The data collected in this study can be used to calculate the number of patients that need to be included in future prospective studies.

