### Strengths and Limitations

Several limitations apply to our study. Since ours is a single-center study, included patients might not fully represent the general population when it comes to age, trauma mechanism, smoking status, and comorbidities. Although as much data as possible concerning baseline characteristics were retrieved, recollection bias could be an issue. Retrospective analyses do not allow for standardized follow-ups and the monitoring of outcome measures, such as fixed-term radiographs and final clinical recovery. However, we will be able to provide an overview of a large period of time to show possible differences in the outcomes of the two historic cohorts. Furthermore, as Dancer’s fractures are relatively rare, it would take several years to include a sufficient number of cases prospectively. With the use of a retrospective design, it is possible to gain a first insight into the outcomes of patients with Dancer’s fractures within a reasonable time frame.

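### Assuming that every patient lost to follow-up was event-free understates both healing-failure rates and, if loss differs between the cohorts, can hide or create the primary difference

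*Protocol article*

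**What the plan says.** The Outcomes section sets the endpoint: "The primary outcome will be the delayed union and nonunion rates in the primary operative treatment group versus those in the conservative treatment group". Under Recruitment, "Delayed union and nonunion are defined as absent or incomplete fracture healing after 3 and 6 months, respectively", and both are judged from radiographs. The same section then fixes how loss is handled: "If patients are lost to follow up, it will be assumed that they did not experience delayed union, nonunion, or other complications". It gives no reason for the rule, no definition of lost, and no expected loss rate.

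Two other statements bear on it. Strengths and Limitations concedes that "Retrospective analyses do not allow for standardized follow-ups and the monitoring of outcome measures, such as fixed-term radiographs and final clinical recovery". Recruitment also plans a telephone contact after consent: "Patients will be asked if they underwent secondary surgery in another hospital". The groups compared are two historic cohorts, conservative for 2012-2015 and operative for 2016-2021 (Study Design and Setting). On size, the Sample Size section says: "It is expected that 236 patients will be included in our study, with approximately 118 in each cohort".

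**The concern.** The rule enters an unknown outcome as a known success and keeps the patient in the denominator. It gives the right answer only if no lost patient had an event. The article's own procedures suggest otherwise: asking about surgery in another hospital recognises that failures may be treated elsewhere, and that question reaches only patients who consent. Because follow-up and films were not standardized, some unknown outcomes should be expected.

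If lost patients had any events, both rates are understated. If the two cohorts lost different shares, the chi-square comparison partly measures completeness of follow-up. They differ in treatment and in calendar period, so equal loss cannot be presumed. At stake are the primary conclusion, the complication counts (covered by the same rule) and the use of these rates to size later prospective studies, which the Sample Size section announces.

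**Working it through.** **Inputs from the article.** 118 per cohort. Delayed union and nonunion of 3% to 9% with nonoperative treatment in the general population, 35% for nonsurgical treatment at age 40 or over, and 4% to 7% after operation (Sample Size). Chi-square test (Statistical Analysis).

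**Assumptions.** Two-sided alpha of 0.05; loss shares m per cohort; lost patients at the same true risk p as those followed. The 15% common rate below is illustrative and not in the article. The 5.5% is the midpoint of 4% and 7%.

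**Reproducing the stated power.** With 9% vs 4%, n = 118 per group, pooled variance and no continuity correction, the normal approximation gives 34.3%, the article's figure. Full binomial enumeration of the uncorrected chi-square test gives 35.4%. The results below use enumeration.

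**Effect of the rule.** Analysed rate = p × (1 − m).

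| True rates (cons. / op.) | Loss (cons. / op.) | Analysed rates | Difference (points) | Rejection probability |
|---|---|---|---|---|
| 9% / 4% | none | 9.0% / 4.0% | 5.0 | 35.4% |
| 9% / 4% | 20% / 20% | 7.2% / 3.2% | 4.0 | 27.7% |
| 9% / 4% | 30% / 10% | 6.3% / 3.6% | 2.7 | 15.1% |
| 9% / 4% | 10% / 30% | 8.1% / 2.8% | 5.3 | 44.0% |
| 9% / 9% | none | 9.0% / 9.0% | 0 | 5.3% |
| 9% / 9% | 30% / 10% | 6.3% / 8.1% | −1.8 | 8.7% |
| 15% / 15% | none | 15.0% / 15.0% | 0 | 5.0% |
| 15% / 15% | 30% / 10% | 10.5% / 13.5% | −3.0 | 10.8% |
| 35% / 5.5% | 30% / 10% | 24.5% / 4.95% | 19.6 (true 29.5) | 99.5% |

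**Equal loss.** The difference becomes (p₁ − p₂)(1 − m). It shrinks but keeps its sign, and with equal true rates no false difference arises.

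**Unequal loss.** With equal true rates the test favours the cohort with more loss. At 15% in both and 30% / 10% loss, 10.4 of the 10.8 percentage points of rejections favour conservative treatment and 0.4 favour surgery. Reversing the loss (10% / 30%) gives the mirror image: 10.4 points falsely favour surgery.

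**The case against.** The strongest defence is that patients who heal stop attending, so scoring the lost as event-free may be close to the truth. That is possible: the bias shrinks as the risk among lost patients falls, and vanishes if all of them healed. But the article neither says this nor gives data for it, and the rule applies it to everyone.

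Several stronger readings are tempting and do not stand.

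- A reader might infer that every patient without a 3- or 6-month film is scored as healed. The rule covers patients lost to follow-up. Someone discharged with documented union before 3 months is not lost and is correctly event-free. The affected share may therefore be well below the 30% used here.
- A reader might infer from the 6 to 8 weeks of immobilization in the Introduction that the conservative cohort had shorter follow-up. That figure describes cited studies, not this hospital. Different periods and treatments make imbalance possible; nothing shows its size or direction.
- A reader might infer that the rule favours the hypothesis that surgery is better. It does so only if more operated patients were lost. With more conservative loss it works against the hypothesis.
- A reader might infer that confidence limits will be too narrow. The Statistical Analysis section specifies a chi-square comparison and no confidence interval for it.
- A reader might think that observed cases alone would cure the problem. If all lost patients healed, a true 15% in both cohorts with 30% / 10% loss would become 15/70 = 21.4% vs 15/90 = 16.7%, a spurious 4.7 points.

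It is also fair that this is a first retrospective look and that the article admits to non-standardized follow-up. That admission does not cover the rule, which is a stated choice and not a detail left to an analysis plan.

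**Conclusion.** The concern holds in a limited form. The article fixes a rule for the primary outcome that is unbiased only if every lost patient healed, and offers no support for that. If lost patients had any events, both rates are understated; equal loss dilutes the difference, and unequal loss can hide or create one.

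The size is unknown because no loss rates are given. Under the assumptions shown, the effect is material at the article's general-population rates: power drops from about 35% to 28% with equal 20% loss, and to about 15% with 30% conservative and 10% operative loss. The false-positive rate roughly doubles, to about 9% to 11%, with 30% vs 10% loss and equal true rates of 9% to 15%. It is not decisive everywhere: a contrast near 35% vs 5.5% keeps 99.5% power at that loss, though its size is understated by about 10 points.

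**What to change.** Drop the event-free assumption as the primary handling, and define lost to follow-up. Count the outcome as known when there is documented radiographic union at any time, a film at or after the 3-month point (delayed union) or the 6-month point (nonunion), or secondary surgery. Otherwise treat it as missing.

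Report the number unknown in each cohort. Analyse with missing outcomes treated as missing: multiple imputation from recorded baseline variables if event numbers allow, otherwise observed cases. The event count may be too small for imputation: 9% and 4% of 118 are about 10.6 and 4.7, or some 15 in all. In either case give best-case/worst-case or tipping-point bounds by cohort, because observed cases alone may overstate rates if healed patients stop attending. Keep the assumed-healed analysis as one labelled sensitivity analysis, and handle complications the same way.

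The cost is a change of wording, modest extra analysis and wider uncertainty. No new patients or procedures are needed.
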